### Standard care (control group)

Participants randomised to the control group will receive usual physiotherapy and ICU standard care, which includes sedation and weaning protocols based on previous publications [32]. Current physiotherapy practice is comparable to the European norm [33] consisting of positioning, respiratory therapy, passive range of movement exercises for nonresponsive patients or active exercises if arousable, and early mobilisation. In order to start as early as possible, physiotherapists screen patients regularly focussing on prevention and treatment of functional and pulmonary impairment. However, subject to our internal procedure, physiotherapy and mobilisation will start after medical prescription. Treatments are based on the therapist’s assessment and are accordingly individually tailored. Sessions will usually take place once daily from Monday to Friday and, if deemed necessary (e.g. severe weakness, intensive rehabilitation and weaning period, retained airway secretion or atelectasis in extubated patients), this includes treatment at the weekend.

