### Study intervention (experimental group)

Patients randomised to the experimental group will receive a standardised exercise programme involving early endurance and resistance training that is combined with early mobilisation. The clinician in charge will decide before study inclusion, whether there are any contraindications to include the patient, and during the study, if at any time the treatment should be stopped, e.g. in case of an adverse event (see safety). Therefore, the intervention will be started as soon as it is deemed safe by the treating ICU team and will occur from Monday to Friday and, if deemed necessary, at the weekend. Throughout all activities, progression will be increased successively, depending on an individual’s tolerance and stability. If needed, the physiotherapist will split the delivery of the exercise programme into one or more sessions (Fig. 2). The number of treatments, its content and duration will be noted for both the control and experimental group.

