**Fig. 2 Fig2:**
[figure not shown]
Daily physiotherapy screening and step progression (experimental group). Legend: ICUAW, Intensive Care Unit Acquired Weakness

Endurance training will be conducted with a motor-assisted bedside cycle ergometer that allows patients to train in a passive, motor-assisted or active mode from a hospital bed (MOTOmed letto2, Reck-Technik, GmbJ & Co. KG, Betzenweiler, Germany) (Fig. 3). Training intensity has been adapted from a previous study with long-term ICU patients from Burtin and colleagues [21]. Thus, the aim for unresponsive patients will be one passive training of 20 min with a fixed pedalling rate of 20 cycles per minute from Monday to Friday. In the course of cycling, patient’s participation will be prompted verbally and by the integrated MOTOmed ServoCycling feature. After achieving patient’s active partaking, the goal will be to train with motor assistance for at least 20 min on level 0. If this is accomplished, assistance will be gradually decreased and subsequently, resistance level and training period increased until a maximum of 60 min on level 6. Tolerance and stability will be judged by the responsible physiotherapist according to patient’s perceived level of exertion (BORG RPE Scale) [34] and especially in unresponsive patients, exceedence of individually set limits. The training position will be supine with an individually adapted head-of-bed elevation to allow for leg movement and comfort.

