### Safety

To ensure the patient’s safety all vital parameters, particularly heart rate, invasive blood pressure and oxygen saturation, will be continuously monitored and recorded by our Patient Data Management System (PDMS), which is routinely checked by the ICU staff. Furthermore, oxygen consumption, energy expenditure and the respiratory quotient by indirect calorimetry will be obtained 30 min prior to, during and for 15 min after physiotherapy. All adverse events (AE) will be noted. These are defined as any event that occurs during or up to 15 min after physiotherapy and persists despite an intervention or therapy interruption. It includes new haemodynamically relevant arrhythmias or otherwise unstable haemodynamics, oxygenation desaturation under 85 %, a fall or other injury as well as any accidental removals of a tube, catheter or similar devices. We use a qualitative physiological approach instead of strict target numbers, as optimal physiological goals for individual patients vary highly and depend on the underlying clinical condition [32]. If a participant exceeds or fails to exceed his individually set limits, the therapist will discontinue the session for the day and will record the reason. If this happens repeatedly, the principal investigator will withdraw the patient from the study. Serious adverse events (SAE) are defined as death, a life-threatening injury or an extension of the length of hospital stay. All SAEs and AEs will be recorded and reported to the principal investigator, who judges their severity and whether they were study-related. All SAEs will also be reported to the local ethics committee. Finally, all occurring complications related to bed rest, such as atelectasis, pneumonia, decubitus ulcer, thrombosis, contracture, delirium and a confirmed critical illness, polyneuropathy or myopathy, will be judged and recorded daily by the treating physician according to our current standard of care.

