### Recruitment, randomisation and blinding

Patients will be screened daily after their ICU admission for study eligibility by the physiotherapist and research nurse in charge and will be included after consultation with the responsible clinician. Reasons for nonrecruitment will be noted in a daily screening log. If a patient is considered eligible a nonparticipating doctor will reexamine the inclusion and exclusion criteria in order to safeguard the patients’ interests according to Swiss law on nonresponsive patients. Participants will then be randomised at a 1:1 ratio to either the experimental or control group by the responsible research nurse using sequentially numbered, opaque, sealed envelopes to ensure a concealed allocation [43]. The allocation sequence was generated in advance by a study nurse using unrestrictive computer-generated randomisation. Furthermore, according to the recommendations of Good Clinical Practice (GCP) the willingness to participate will be obtained in the form of a presumed consent from the patients’ proxy within 72 h (Table 1). After regaining the power of judgement, patients will be informed of the study in writing and asked retrospectively by a GCP-trained physician to provide written informed consent. Participants have the right to withdraw from the trial at any given time. If unwilling to participate or withdrawing from the trial, patients will be excluded from the study and asked if the data that has already been collected may be retained. The sample size will be adjusted for dropouts.

Due to the nature of the intervention it is not possible to maintain blinding for the treating physiotherapists, ICU staff or participants. However, the group of physiotherapists who will assess the main outcomes will be distinct from the treating therapists and will, therefore, be blinded to group allocation.

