### Statistical analysis

Study data will be analysed as randomised with SPSS (IBM SPSS Statistics Version 21) by both intention-to-treat (main analysis) and per-protocol analysis. However, the intention-to-treat analysis will only include participants with an informed consent, as adjusted in the sample size calculation. The level of significance will be set at *p* < 0.05. Descriptive statistics will be used to describe mean outcomes and distribution. Subsequently, the outcome parameters between the two groups will be compared using Student’s *t* tests for normally distributed data and the Mann-Whitney *U* test for nonnormal distribution. For repetitive data repeated measures analysis of variance (ANOVA) will be deployed and for correlations between variables the Spearman correlation coefficients or similar will be used. If missing data are more than 5 %, multiple imputations will be performed. There will be one planned interim analysis after enrolment of 35 patients for assessment of safety.

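### Repeated breaches of individual limits end study participation, not only training, so primary outcomes can go missing in relation to tolerance, at odds with the as-randomised analysis

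*Protocol article*

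**What the plan says.** Three parts of the protocol article bear on this.

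- **Safety.** The trigger is worded for any participant, and the cause of each stop is noted: "If a participant exceeds or fails to exceed his individually set limits, the therapist will discontinue the session for the day and will record the" […]. The next sentence gives the consequence of recurrence: "If this happens repeatedly, the principal investigator will withdraw the patient from the study". Neither the limits nor the number of recurrences is quantified. On the limits the article is explicit: "We use a qualitative physiological approach instead of strict target numbers".
- **Study intervention (experimental group).** Here the clinician in charge decides "if at any time the treatment should be stopped, e.g. in case of an adverse event (see safety"). Leaving the study is not mentioned.
- **Statistical analysis.** "Study data will be analysed as randomised", with intention-to-treat as the main analysis. The only exclusion named is absence of informed consent. Multiple imputation is planned if more than 5% of data are missing.

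Both primary outcomes are measured at hospital discharge (Outcome; Table 1), whereas the rule operates during physiotherapy in the ICU. The only text on what follows departure from the trial is under Recruitment, randomisation and blinding. It concerns patients who refuse or withdraw themselves: they are excluded and asked about data already collected.

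**The concern.** Stopping an intervention and leaving a trial are different events. An intention-to-treat comparison depends on measuring outcomes in patients who had the first without the second. The rule merges them for a group selected after randomisation by poor physiological tolerance, which plausibly goes with shorter walking distance and less independence. The staff who end sessions know the allocation; the article says "it is not possible to maintain blinding for the treating physiotherapists, ICU staff or participants".

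If withdrawals fall unevenly between arms, the arm that loses more patients keeps its better tolerators, and the 6MWT and FIM comparison moves in its favour. Safety is also involved. The article hypothesises that training is as safe as standard therapy, and serious adverse events after withdrawal, such as death or a prolonged hospital stay, may go unrecorded in the patients of most interest.

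**Working it through.** **1. The plan's own figure.** Inputs from Sample size: difference 54 m, SD 81 m, power 80%, α 0.05 (taken as two-sided).

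n per arm = 2 × [81 × (1.960 + 0.842) / 54]² = 35.3, rounded up to 36, so 72 in total. Adding 14 per arm gives 100, and adding 15 for dropout gives 115. The stated size reproduces, so the point does not rest on a sample size error. The dropouts that the section names are refusals of consent; safety withdrawals are not mentioned.

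**2. The passages together.** Take a patient who has consented and is then withdrawn under the safety rule. By the statistical section this patient belongs to the intention-to-treat set. By the safety section the patient has left the study before hospital discharge. Nothing in the article says that follow-up continues. The patient is therefore in the analysis set with both primary outcomes missing, and the reason for the missingness is tolerance.

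**3. Exposure by arm.** The experimental arm has cycling with "resistance level and training period increased until a maximum of 60 min on level 6", plus resistance training, on top of mobilisation. The control arm has "passive range of movement exercises for nonresponsive patients or active exercises if arousable, and early mobilisation". Both arms can trigger the rule. The added load makes more triggers in the experimental arm plausible, but the article does not say so.

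**4. Illustrative size on the 6MWT.** The article gives no withdrawal rate, so these inputs are assumptions: the least tolerant share w leaves the experimental arm, none leave the control arm, tolerance and 6MWT correlate at ρ, there is no true effect, and the patients who remain are compared. There are 36 + 14 = 50 per arm before withdrawal.

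Shift in mean = 81 × ρ × φ(z_w) / (1 − w), where z_w is the normal quantile at w.

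SE = 81 × √(1/[50(1 − w)] + 1/50), with the SD kept at 81 m as an approximation. Type I error = 1 − Φ(1.96 − shift/SE) + Φ(−1.96 − shift/SE).

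| w | φ(z_w)/(1 − w) | ρ = 0.3 | ρ = 0.5 | ρ = 1 | Type I error, ρ 0.3 to 0.5 |
|---|---|---|---|---|---|
| 5% | 0.109 | 2.6 m | 4.4 m | 8.8 m | 0.053 to 0.058 |
| 10% | 0.195 | 4.7 m | 7.9 m | 15.8 m | 0.059 to 0.076 |
| 15% | 0.274 | 6.7 m | 11.1 m | 22.2 m | 0.068 to 0.101 |

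Example: 81 × 0.5 × 0.274 = 11.1 m; SE = 81 × √(1/42.5 + 1/50) = 16.9 m; ratio 0.66; type I error 0.101.

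Against the 54 m target: 2.6/54 = 5% and 11.1/54 = 21%. The ρ = 1 column is an upper bound; 22.2/54 = 41%.

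With 15% removed from the experimental arm and 5% from the control arm, the bias is 4.0 to 6.7 m and the type I error 0.056 to 0.068. With 10% removed from each arm, the bias in this null model is zero.

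**5. Imputation threshold.** If only these withdrawals were missing, 5% of one arm is 2.5 of 100 patients (2.5%), 10% is 5 of 100 (5%, not above the threshold) and 15% is 7.5 of 100 (7.5%). Withdrawals alone would therefore reach imputation only at the upper end. Other missing data could take the total past 5% sooner.

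The article gives no SD or target difference for the FIM, so no size is computed for it.

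**The case against.** Several stronger readings suggest themselves, and the article does not support them.

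- **A reader might infer that the rule removes patients from the intention-to-treat analysis.** It does not say so. Lack of consent is the only stated exclusion, a 15% dropout allowance exists, and imputation is planned above 5% missing. The defect is informative missing data, not a demonstrated exclusion. That correction stands in full. Imputation in its usual missing-at-random form would still not by itself remove bias from tolerance-driven withdrawal.
- **A reader might infer that withdrawals come mostly from the trained arm.** The rule covers both arms. Control session length is not given, so longer experimental sessions are not documented. Progression follows individual tolerance, the programme may be split over sessions, and unresponsive patients begin with passive cycling. All of this should reduce breaches. The imbalance remains plausible but unproven.
- **A reader might infer that harm is under-recorded in general.** The events that trigger the rule are captured before withdrawal: reasons for stopping are recorded, adverse events are noted, and vital parameters are logged continuously. Adverse events are defined around physiotherapy sessions. Only later events, chiefly serious ones, are at risk.
- **A reader might take about 22 m as the likely inflation.** That needs a correlation of 1, the worst 15% removed and no control withdrawals.

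It can also be said that a journal article condenses a fuller protocol, which may provide for follow-up after an investigator's withdrawal. Silence on that procedure would be no finding. But the article does state the rule, and states it as leaving the study, while another section speaks only of stopping treatment. That inconsistency lies in the text shown.

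**Conclusion.** The point holds as a conflict between three sections that must be reconciled. Under the rule as written, primary outcomes are lost for a reason related to tolerance, by a process begun by staff who know the allocation, and nothing in the article keeps these patients in follow-up.

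The size is unknown. Under one-sided removal of 5% to 15% and moderate correlation, it is about 3 to 11 m on the 6MWT, with type I error rising from the nominal 0.05 to at most about 0.10. It shrinks as withdrawals become more balanced and vanishes under the null when they are equal. These figures rest on assumed withdrawal shares and correlations and on comparing only the patients who remain. They show that the effect could matter; they do not estimate what happened. If the sponsor meant only that training stops, the correction is a clarification.

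**What to change.** Reconcile the three sections without altering when a session or training is stopped, which is a clinical matter. State that, in either arm, a stop under the safety rule ends the study intervention only and not study participation. Such patients keep every scheduled assessment (ICU discharge, hospital discharge, 6 months) and serious adverse event recording where consent allows, and are analysed in their allocated arm.

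The planned size stays at 115, and the assessments are already in Table 1, so the cost for future patients is a short amendment.

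The change comes late. Randomisation began in October 2012, recruitment was due to finish in February 2016 and the study in August 2016, so hospital-discharge tests already missed cannot be repeated. For patients already withdrawn, pursue available outcomes where consent allows, report numbers and reasons by arm, and add a sensitivity analysis in which their outcomes are not missing at random. This needs some record retrieval and one further analysis.

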### Outcome

The primary outcome measures are functional capacity using the 6-Minute Walk Test (6MWT) [35] and the ability to perform activities of daily living using the Functional Independence Measure (FIM) [36]; both will be evaluated at hospital discharge.

The secondary outcome measures were chosen to reflect the physical impairment after ICUAW and whether these important clinical outcomes can be improved by early training. They are as follows:

Muscle strength and ICUAW diagnosis at ICU discharge: Medical Research Council sum score [5, 37], handgrip strength using the JAMAR dynamometer (Sammons Preston Rolyan, Bolingbrook, IL, USA) [37, 38] and quadriceps muscle strength using a handheld dynamometer (Microfet 2, Biometrics, Almere, Netherlands) [38]. Muscle strength tests will only be performed if a patient can follow three out of five simple commands in order to assess their ability to cooperate as well as the level of consciousness beforehand [39].

Joint contractures, which are defined as limitations in range of motion, will be recorded after ICU discharge for the following joints: shoulder flexion, elbow flexion and extension, fist closure, hip flexion, knee flexion and extension and foot dorsiflexion [40].

Functional mobility will be measured with the Timed ‘Up & Go’ Test [41] at hospital discharge.

The quality of life 6 months after hospital discharge will be assessed with the Short Form 36 (SF-36, version 1.3) [42].

The overall time on mechanical ventilation, length of stay in the ICU and the hospital, as well as achieved milestones during the ICU stay (sitting on the side of the bed, sitting in a chair, standing or walking) will be reported.

Furthermore, the safety of early training, particularly the physiological response of the participants, any occurring AE, SAE and other complications related to bed rest as well as the feasibility, frequency, duration and content of the therapy, will be collected and analysed.

The schedule for the outcome assessments is shown in Table 1.

**Table 1 Tab1:** Schedule for enrolment, data collection, interventions and outcome measures

	Enrolment	Allocation	Post allocation			
Timepoint	ICU admission		ICU stay (daily)	ICU discharge	Hospital discharge	6-month follow-up
Enrolment:						
Eligibility screen	x					
Consent by nonparticipating doctor	x					
Allocation		x				
Informed consent by proxy		≤72 h				
Data collection:						
Demographic and diagnostic data		x				
APACHE II score	x					

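### Read as written, the SAE definition leaves out life-threatening arrhythmia, haemodynamic instability, desaturation or device loss that is survived without a longer hospital stay, so these events have no stated route to the ethics committee

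*Protocol article*

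**What the plan says.** Everything needed is in the Safety section of the protocol article, apart from one line under Outcome.

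- **AE definition.** "These are defined as any event that occurs during or up to 15 min after physiotherapy and persists despite an intervention or therapy interruption".
- **AE examples.** "It includes new haemodynamically relevant arrhythmias or otherwise unstable haemodynamics, oxygenation desaturation under 85 %, a fall or other injury". The sentence ends with the device items: "a fall or other injury as well as any accidental removals of a tube, catheter or similar devices".
- **SAE definition.** "Serious adverse events (SAE) are defined as death, a life-threatening injury or an extension of the length of hospital stay".
- **Internal route.** "All SAEs and AEs will be recorded and reported to the principal investigator, who judges their severity and whether they were study-related".
- **External route.** "All SAEs will also be reported to the local ethics committee".
- **Analysis.** Under Outcome, the safety data to be collected and analysed include "any occurring AE, SAE and other complications related to bed rest".

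The article has no other SAE definition, and no sentence turns a severe AE into an SAE.

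**The concern.** The life-threatening limb of the SAE definition is attached to injury, not to any event. The AE list in the same section uses injury for a narrower class: it is paired with falls and stands beside the cardiac, circulatory, respiratory and device items. Where the authors mean any occurrence, they write 'event', as in the AE definition. On the section's own vocabulary, then, the life-threatening criterion covers the class that includes falls and leaves out the classes that the monitoring watches most closely (heart rate, invasive blood pressure, oxygen saturation).

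Safety is part of the study purpose, and one secondary hypothesis is that the training is as safe as standard therapy. If survived life-threatening cardiorespiratory or device events are not counted as SAEs, the SAE comparison between arms is less informative on that hypothesis. The ethics committee also does not receive those events through the only external reporting route the article states.

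**Working it through.** No arithmetic applies. The check sets the definitions side by side and follows one event through them.

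**Step 1: which listed AE types can meet each SAE limb.** The AE sentence yields five types: arrhythmia, unstable haemodynamics, desaturation, fall or other injury, and accidental device removal.

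| AE type | Death | Life-threatening injury | Extended hospital stay |
|---|---|---|---|
| Arrhythmia | yes | no | yes |
| Unstable haemodynamics | yes | no | yes |
| Desaturation | yes | no | yes |
| Fall or other injury | yes | yes | yes |
| Device removal | yes | no, unless it also causes an injury | yes |

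One type of five reaches the life-threatening limb directly. The other four become SAEs only through death or a longer stay. This count restates the wording; it says nothing about how often such events occur.

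**Step 2: follow a life-threatening arrhythmia, circulatory collapse or desaturation during a session.**

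- (a) Fatal: an SAE, reported to the ethics committee.
- (b) Survived, hospital stay extended: an SAE, reported to the ethics committee.
- (c) Survived, stay not extended, persists despite intervention or interruption: an AE only. It goes to the principal investigator and into the safety analysis, with no stated route to the ethics committee.
- (d) Survived, stay not extended, resolves with intervention or interruption: not an SAE, and it also fails the persistence condition in the AE definition. Read literally, it is neither.

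The gap consists of (c) and (d). Cases (a) and (b) are handled.

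**Step 3: does another sentence close the gap?** The principal investigator judges severity and relatedness, but nothing links that judgement to SAE status or to the ethics committee. The section also says that the therapist records the reason when a session is discontinued because individual limits were not respected, and that vital parameters are recorded continuously in the PDMS. These leave a trace of events of type (d), but neither provision classifies or reports them.

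**Step 4: what this means for a remedy.** Re-reading AE forms recovers events of type (c). It can miss type (d), because those events need never have been entered as AEs. The session-stop reasons and the PDMS record are needed for them.

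**The case against.** Four points can be made on the other side.

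**The definition still catches much.** A reader might infer that a life-threatening arrhythmia, collapse or desaturation is never an SAE and never reaches the ethics committee. The text does not support that: if it is fatal or extends the stay, it is an SAE and is reported. This stands, and it confines the point to cases (c) and (d).

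**Events outside the SAE definition are not lost.** A reader might infer that such events are seen by the principal investigator alone. That is also too strong. AEs are analysed as well as SAEs, one interim analysis for safety is planned after 35 patients, ICU staff routinely check the PDMS, and its data are kept for further safety analysis. This stands. These routes are internal, however, so they do not replace reporting to the ethics committee. For case (d), only the raw record and the session-stop reason remain.

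**Injury may simply mean harm.** The article states adherence to GCP and Swiss law, and the full protocol or the reporting forms may be worded more broadly. That is possible and cannot be settled from the article. But the article states the definition outright, so this is not a detail left to a fuller document, and its own AE list supports the narrower reading.

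**The change comes late.** Under Trial status, recruitment was expected to finish by the end of February 2016 and the study in August 2016, the month of publication. A wording change would therefore govern few or no new sessions. This stands: the practical gain lies in reclassifying events already on record.

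**Conclusion.** The point holds in a limited form. As written, the SAE definition and the AE list do not fit together. Life-threatening events that are not injuries, and are survived without a longer stay, fall outside the SAE definition and have no stated route to the ethics committee. If they resolved with intervention or interruption, they may fall outside the AE definition too.

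Four of the five listed AE types are affected. How many patients that means cannot be said, because the article gives no event rates; it may be none. No endpoint, sample-size figure or efficacy analysis is touched.

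The conclusion rests on two assumptions: that injury in the SAE sentence carries the meaning it has in the AE list, and that those classifying events followed the published wording. If the working forms already used a broader definition, the correction is to the article's text only. The change is worth making because safety is a stated aim and the correction is cheap.

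**What to change.** 1. Reconcile the SAE definition with the AE list: replace 'a life-threatening injury' with 'any life-threatening event', and state that this applies whether or not the event resolved with intervention or interruption.
2. Before the safety analysis, apply this definition in the same way to both arms, using three sources: recorded AEs, the recorded reasons for discontinued sessions, and the PDMS data. AE forms alone are not enough, because of the persistence condition.
3. Report any reclassified events to the ethics committee, and state in the safety results that the reclassification was done.

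The cost is one phrase in the text, some additional record review (the PDMS screen is probably the largest part) and possibly a few more SAE reports. The change concerns classification and reporting only; it alters nothing in how patients are treated or sessions are run.

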### Hypotheses

The primary hypothesis is that critically ill, mechanically ventilated adults who participate in an early endurance and resistance training, combined with early mobilisation, have an improved functional capacity and are, therefore, more functionally independent at hospital discharge compared to patients receiving the usual physiotherapy care. Secondary hypotheses are that this early training is as feasible and as safe as standard therapy. Further, we expect improvements in muscle strength at ICU discharge, fewer joint contractures, less time on mechanical ventilation, a shorter length of stay in the ICU and the hospital, and a higher quality of life at 6 months after hospital discharge compared to patients receiving usual care.

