### Study duration

The study intervention will take place during the entire ICU stay as well as during potential readmissions to the ICU. Therefore, the study duration will be variable for each patient. After ICU discharge both groups will receive the usual physiotherapy treatment and, if necessary, rehabilitation. Likewise, there will be no difference for participants of both groups in terms of medical attention, treatment and care during the whole study duration. The study will finish with a follow-up 6 months after hospital discharge.

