SOFA score			x			
TISS 28 and 76	x			x		
Laboratory findings	x	x		x		
Medication			x			
Physiotherapy Interventions:						
Frequency, duration and content			x			
Safety and physiological parameters			x			
Mobility milestones			x			
Bed rest complications			x			
Serious/adverse events			x			
Outcome measures:						
Muscle strength: MRC sum score, handgrip and quadriceps strength				x		
Range of motion				x		
Functional Independence Measure				x	x	
Length of stay (ICU and hospital), days on mechanical ventilation					x	
6-Minute Walk Test					x	
Timed ‘Up & Go’ Test					x	
Short Form 36						x

*APACHE* Acute Physiology and Chronic Health Evaluation, *ICU* intensive care unit, *MRC* Medical Research Council, *SOFA* Sequential Organ Failure Assessment score, *TISS* Therapeutic Intervention Scoring System

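### Bed-rest complications are recorded only on ICU days, so a raw comparison by arm can favour training merely because recording stops earlier

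*Protocol article*

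**What the plan says.** The Safety section of the protocol article lists "complications related to bed rest, such as atelectasis, pneumonia, decubitus ulcer, thrombosis, contracture, delirium" and confirmed critical illness polyneuropathy or myopathy. It says that these "will be judged and recorded daily by the treating physician according to our current standard of care". That sentence gives no end date.

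Table 1 (Outcome section) supplies one. The row "Bed rest complications", in the block on physiotherapy interventions, has a single mark, in the column for daily recording during the ICU stay. Nothing is marked at ICU discharge, hospital discharge or six months. The row for serious and other adverse events has the same single mark.

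The Hypotheses section predicts "less time on mechanical ventilation, a shorter length of stay in the ICU and the hospital" with training. The Study duration section ties the intervention phase to the ICU stay and any ICU readmissions, and adds: "Therefore, the study duration will be variable for each patient".

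The Outcome section includes "any occurring AE, SAE and other complications related to bed rest" among the safety data to be collected and analysed. It also provides separate assessments of range of motion and of ICU-acquired weakness, at or after ICU discharge in both arms.

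**The concern.** Each patient is observed for these complications for as long as he or she is in the ICU. If the length-of-stay hypothesis is right, trained patients are observed for fewer days. A ward pneumonia or thrombosis after an earlier ICU discharge has no scheduled place in the data, while the same event on the same day after randomisation in a control patient still in the ICU would be counted.

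A lower recorded frequency with training could then be read as prevention, or as reassurance on safety, when part of it comes from a shorter window. ICU death closes the window as well. More early deaths in one arm would lower that arm's recorded complications, whichever arm it is.

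**Working it through.** The document gives no complication rate, no expected ICU stay and no expected reduction in stay, so there is no figure of its own to reproduce. Its sample size concerns the 6-Minute Walk Test and does not bear on this point. What follows illustrates the mechanism.

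**Inputs from the document.** Recording on ICU days only (Table 1); a shorter ICU stay expected with training (Hypotheses).

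**Assumed inputs.** The same daily hazard h in both arms, with h = 0.02, 0.05 or 0.10; an ICU stay L of 10 days in controls and 8 days with training.

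**Step 1, every patient in an arm stays L days.** Recorded risk = 1 − exp(−hL). Differences are taken before rounding.

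| h per day | Control, L = 10 | Trained, L = 8 | Difference | Risk ratio |
|---|---|---|---|---|
| 0.02 | 1 − exp(−0.20) = 18.1% | 1 − exp(−0.16) = 14.8% | 3.3 points | 0.82 |
| 0.05 | 1 − exp(−0.50) = 39.3% | 1 − exp(−0.40) = 33.0% | 6.4 points | 0.84 |
| 0.10 | 1 − exp(−1.00) = 63.2% | 1 − exp(−0.80) = 55.1% | 8.1 points | 0.87 |

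Daily risk is identical by construction, so the whole difference comes from the window.

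**Step 2, stays vary between patients.** With an exponential stay of mean L, recorded risk = hL/(1 + hL):

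- h = 0.02: 0.20/1.20 = 16.7% versus 0.16/1.16 = 13.8%, a difference of 2.9 points.
- h = 0.05: 0.50/1.50 = 33.3% versus 0.40/1.40 = 28.6%, a difference of 4.8 points.
- h = 0.10: 1.00/2.00 = 50.0% versus 0.80/1.80 = 44.4%, a difference of 5.6 points.

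The artefact is somewhat smaller and in the same direction.

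**Step 3, risk falls late in the stay.** Suppose h = 0.05 for eight days and half that on the last two. The control cumulative hazard is 8 × 0.05 + 2 × 0.025 = 0.45, so the control risk is 1 − exp(−0.45) = 36.2%. Against 33.0% with training the difference is about 3 points, roughly half the value in Step 1.

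**Step 4, a wider range.** For control stays of 7, 10 or 14 days, trained stays 1 to 3 days shorter and the same three hazards, the fixed-stay risk ratio runs from 0.59 (h = 0.02, 4 versus 7 days: 7.7% versus 13.1%) to 0.97 (h = 0.10, 13 versus 14 days: 72.7% versus 75.3%).

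**Step 5, counts and rates.** The expected event count is hL, so at 8 versus 10 days the count ratio is 8/10 = 0.80. Dividing by ICU days gives h in both arms, a ratio of 1.00.

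**Step 6, chance of a nominally significant result.** With 50 per arm (36 + 14 in the Sample size section), 33.0% versus 39.3% would reach p < 0.05 about 10% of the time. Over the range in Step 4 the chance is about 4% to 42%. The usual harm is a shifted estimate and not a false significant finding.

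**The case against.** The strongest case on the other side has five parts.

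- **The analysis is left open.** A reader might infer from the Statistical analysis section that raw proportions will be compared. It names t tests and Mann-Whitney tests and no test for yes/no events, so the document does not commit to that. An analysis plan that is not at hand may already use rates per ICU day. This stands. It does not reach ward events, which no analysis can recover if they were never collected, and the collection window is fixed in Table 1.
- **No general claim of prevention is made.** A reader might infer that a claim about bed-rest complications becomes untestable. The Hypotheses section predicts fewer joint contractures, and otherwise only that training matches standard therapy on safety. Contracture and ICU-acquired weakness have their own assessments at or after ICU discharge. This also stands, and it confines the point to pneumonia, atelectasis, decubitus ulcer, thrombosis and delirium, reported as safety data.
- **Part of the difference is real.** If ward risk is lower than ICU risk, fewer ICU days do mean fewer complications. That is fair. A raw ICU proportion is a legitimate description provided it is labelled as one.
- **The size is assumed throughout.** That is true, and constant hazard is the less favourable assumption for the plan: Step 3 shows the artefact roughly halving when late risk is halved.
- **Other routes might catch ward events.** Readmission extends recording only for those readmitted. The adverse-event row in Table 1 is also confined to the ICU stay, and the Safety section limits adverse events to physiotherapy and the 15 minutes after it. This part does not stand.

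**Conclusion.** The point holds in a limited form. Table 1 ties recording to ICU days and the Hypotheses section expects training to reduce those days. Raw counts or proportions of pneumonia, atelectasis, decubitus ulcer, thrombosis and delirium can therefore favour training without any difference in daily risk. If mortality differs between arms, truncation by ICU death could push the comparison either way.

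The 3 to 8 points are an illustration that rests on an equal constant hazard of 0.02 to 0.10 per day and 10 versus 8 ICU days. They should not be read as the bias expected in this trial: the document supplies none of these inputs, and both variable stays and falling risk reduce the figure. The primary endpoints are not touched. This is a cheap improvement to the safety reporting and not a defect that undermines the trial.

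**What to change.** 1. Report these five complications as events per ICU day at risk, from a count model with log ICU days (readmission days included) as offset, beside the raw proportions. Describe both as ICU-period events. ICU length of stay is already collected.
2. Where hospital records allow, also count events to the same fixed day after randomisation in both arms, with death as a competing event. Choose that day before the arms are compared.
3. Do not take hospital discharge as the common period, because the Hypotheses section expects the hospital stay to shorten too.

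The cost is one extra model and some chart abstraction. The Trial status section expected recruitment to end in February 2016, so the second step would rest on existing records and not on a new recording schedule. Ward ascertainment is likely to be less systematic than daily ICU review and may cover more days in the trained arm, so the fixed-day count has its own weakness. A rate per ICU day assumes roughly constant daily risk. It therefore supports the raw figures and does not replace them.
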